### **6.3 Blinding**

The study is planned as open label study. Trial subjects and investigator will be aware of treatments received as whether subject is taking Euvichol-Plus or Shanchol.

### **6.4 Randomization**

Randomization will be done in the Cohort 1 and 2, each comprising of 208 healthy subjects. Each cohort will have two study arms, comprising 104 healthy subjects enrolled into each treatment arm. The enrolled subjects will be randomly allocated in a 1:1 ratio to receive either of the following:

- Euvichol-Plus
- Shanchol

Biostatistician will prepare the randomization list for the study available resources to prevent biasness. After confirmation that the subject meets the eligibility criteria for enrolment in the clinical trial, Subjects would be assigned a randomization number sequentially in the order in which they enter the study by the Investigator.

**Figure 1 Flow diagram for randomization**

[figure not shown]

**6.5 Expected Duration of Study:**

Approximately 7-8 months from the date of study initiation.

**6.6 Duration of Protocol therapy**

4 weeks (2 vaccinations, each 2 weeks apart with a window period of 3 days at each dose).

**6.7 Duration of Subject Participation:**

Each subject will have a total of 5 study visits, which are as follows:

- Visit 1: Screening Enrolment and First Vaccination (Day 0)
- Follow Up 1 (Telephonic Visit)
- Visit 2: Second Vaccination Visit (Day 14 + 3)
- Follow Up 2 (Telephonic Visit)
- Visit 3: End of Study (EOS) Visit (Day 28 + 3)

## **STUDY FLOWCHART**

[figure not shown]

## **7.0 SELECTION AND WITHDRAWAL OF SUBJECTS**

### **7.1 Inclusion Criteria**

1. Individuals aged 1 year to 60 years both inclusive
2. Voluntary written informed consent form for study participation provided by an individual or his/her legally acceptable representative. Subjects aged 12 to <18 years, must sign an assent for the study and a parent or a legal guardian have to sign the informed consent. Subject aged 7 to 11 years need to provide an oral consent/assent and the consent form must be signed by parent/legally acceptable representative. Less than 7 years no need of assent, LAR can give consent.
3. An individual who can be followed up during the study period and is capable of complying with the study requirements.
4. Healthy subjects as determined by: Medical history, Physical examination and Clinical judgment of the investigator

### **7.2 Exclusion Criteria:**

Any one of the following

1. History of cholera vaccinations or history of cholera.
2. History of hypersensitivity reactions to other preventative vaccinations.
3. Immune function disorders including immunodeficiency diseases.
4. 38°C or higher body temperature measured prior to investigational product dosing.
5. Diarrhea or abdominal pain lasting 2 weeks or longer within 6 months prior to study initiation. Also, administration of antidiarrheal drugs or antibiotics to treat diarrhea within 1 week prior to study initiation.
6. Abdominal pain, nausea, vomiting, or decreased appetite within 24 hours prior to study initiation.
7. Pregnant or lactating women.
8. Children vaccination within 1 month prior to study initiation or planned vaccination during the study.
9. Participation in another clinical trial with investigational product dosing within 6 months prior to study initiation.
10. An individual thought to have difficulty in participating in the study due to severe chronic diseases, based on the judgment of the investigator.

11. An individual thought to have difficulty participating in the study due to other reasons, based on the judgment of the investigator.
12. If female patient will get pregnant after first vaccination

### **7.3 Withdrawal of Subjects**

Subjects will be discontinued or withdrawn from the study in case of following scenarios:

1. If the subject requests discontinuation or withdraws consent.
2. If the subject experiences a serious adverse event (SAE) which makes him/her incapable of further participation in the study.
3. Any entry criteria are violated, and the violation becomes apparent during the course of the study.
4. In case where the subject does not meet the inclusion and exclusion criteria, withdraws the informed consent or when a subject is required to be withdrawn solely at the discretion of investigator.
5. Subject does not report to the hospital for any of the 2 vaccination days or follow up visit beyond the allowable window period (+3 days) for blood withdrawal for the immunogenicity testing.
6. The subjects will be excluded from the second dose, If Life-threatening allergic reaction after a previous dose of any cholera vaccine or if female subject gets pregnant after first vaccination.
7. If there is a significant change in the vital signs, physical examination considering the safety of the subject.

In the event of withdrawal of a subject, the investigator shall assess the primary cause for the subject's withdrawal and document this in the Source and Case Report Form (CRF).

Subjects will be informed that they have the right to withdraw from the study at any time, without prejudice to their medical care, and that they are not obliged to state their reasons. Any withdrawal must be fully documented in the CRF and source documents. The investigator may also withdraw a subject at any time if this is considered to be in the subject's best interest.

Subjects withdrawn from the study will not be replaced.

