## **5.4 Subjects Compliance**

Window period of +3 days will be allowed for visit 2, and visit 3. Subjects not reporting to the hospital or reporting late by more than 3 days for second dose of vaccination or post vaccination follow-up visit after second dose will be excluded from immunogenicity analysis. All the subjects receiving at least 1 dose will be included in safety analysis.

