## **5.7 Concomitant Medication**

All concomitant medication, including non-study medicines, being taken by the subjects at enrolment and during this clinical trial are to be regarded as concomitant medications and must be documented on the “Concomitant Medications Record” section of CRF.

Antipyretic medication (Paracetamol) may be administered in case of fever, but prophylactic use of antipyretic medication is not permitted. In case if any other medication is administered to the subject during the course of the study, the decision to continue or discontinue the subject in the study would be taken by the investigator in consultation with sponsor. The decision would be based on whether the administered medication is known to interfere with the immune response.

The following concomitant treatments are discouraged and, if used, will lead to subject's withdrawal during this study (see exclusion criteria as well):

1. Systemic steroids
2. Other immune-suppressive agents
3. Blood or plasma derivatives including immunoglobulin.

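### Section 7.3 withdraws dosed subjects from the study for a missed blood-sampling window or a late-found entry violation, and no text expressly keeps them in adverse-event collection to Day 28

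*Supplement*

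**What the plan says.** Section 7.3 introduces seven items with "Subjects will be discontinued or withdrawn from the study in case of following scenarios". Those that matter here are:

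- **Item 5:** "Subject does not report to the hospital for any of the 2 vaccination days or follow up visit beyond the allowable window period". The item goes on to give the window as +3 days and to tie it to the blood sample for immunogenicity testing.
- **Item 3:** an entry criterion was violated and this comes to light during the study.
- **Item 7:** "If there is a significant change in the vital signs, physical examination considering the safety of the subject".
- **Item 6**, by contrast, is worded as a stop to dosing only: "The subjects will be excluded from the second dose, If Life-threatening allergic reaction after a previous dose of any cholera vaccine", or pregnancy after the first dose.

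At withdrawal, section 7.3 asks the investigator to establish the main cause and document it. It names no early-termination visit and no further safety contact.

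Section 5.7 lists systemic steroids, other immunosuppressants and blood or plasma derivatives, introduced by: "The following concomitant treatments are discouraged and, if used, will lead to subject's withdrawal during this study".

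Section 5.4 deals with the same window deviation as item 5. It excludes "Subjects not reporting to the hospital or reporting late by more than 3 days for second dose of vaccination or post vaccination follow-up visit" (the visit after the second dose) from the immunogenicity analysis, and it keeps everyone with at least one dose in the safety analysis. Section 12.0 defines the safety set in the same way. Section 4.8 sets unsolicited adverse events and SAEs over Day 0 to Day 28.

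**The concern.** A subject who has swallowed a dose, has not withdrawn consent and has no safety reason to leave can be taken out of the study because a blood sample fell outside its window. The subject still counts in the safety denominator for an endpoint that runs to Day 28, but nothing obliges the site to ask about new events after withdrawal. The same holds for a subject whose entry violation is found late or who takes a medication listed in 5.7.

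Safety comparison is the trial's secondary objective (4.7). What is at stake is incomplete adverse-event ascertainment in subjects who are counted as assessed. For item 5 the loss is avoidable, because the reason given for withdrawal concerns immunogenicity and section 5.4 already deals with it.

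The wording also leaves sites unsure. Visit 2, item d, in section 8.1 uses the 7.3 list as the check before the second dose, while 7.3 itself speaks of leaving the study.

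**Working it through.** No stated figure needs reproducing. The check sets the passages side by side.

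**Step 1: one deviation, two consequences.** For attendance more than 3 days late, section 5.4 gives exclusion from the immunogenicity analysis and retention in the safety analysis. Section 7.3 item 5 gives withdrawal from the study. Section 5.4 alone is enough to protect the immunogenicity analysis. If the second dose should not be given late, stopping the dose is enough for that.

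**Step 2: does any passage keep a withdrawn subject in collection of new adverse events?**

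| Section | What it provides | Covers new events after withdrawal? |
|---|---|---|
| 3.0, Endpoints | Safety assessed from enrolment to the end of the study period | General; silent on withdrawn subjects |
| 3.0, Study Methodology; Table 1 | Calls for 3 days after each dose; diary recording | No |
| 5.3 | Two weeks of planned follow-up after each vaccination | General; does not say it survives withdrawal |
| 8.1, telephone visits | Contact by e-mail, phone or visit, no duration given | Silent on withdrawn subjects |
| 8.1, Visits 2 and 3 | Adverse-event review and diary collection at the visit | Only if the visit takes place |
| 10.2 | Adverse events recorded until the last study visit; events that have occurred are followed | Last study visit is not defined for a withdrawn subject |
| 10.5 | Existing adverse events and SAEs followed up | Existing events only |
| 5.4, 12.0 | Who is in the safety analysis | Decides who is analysed, not what is collected |
| 9.0 | Sponsor confirms continuation or withdrawal after a deviation | Case-by-case discretion, not a rule |

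None does so expressly.

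**Step 3: what is lost, by case** (Visit 1 as Day 0, as in section 6.7).

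- *Late at Visit 2 (item 5).* The window closes on Day 14 + 3 = Day 17. The endpoint period ends on Day 28, leaving 28 − 17 = 11 days of that period with no stated collection. The two weeks after dose 1 (5.3) have already passed, and they are covered if the adverse-event review is done at the late visit.
- *Late only at Visit 3 (item 5).* The window closes on Day 28 + 3 = Day 31, after the endpoint period. What may be lost is the final inquiry, examination and diary collection.
- *Item 3 or section 5.7.* Withdrawal can come at any time after dosing, so the loss depends on when it happens.
- *Items 2 and 7.* The triggering SAE, or a change that counts as an adverse event, is followed under 10.2 and 10.5. Item 7 changes would generally be found at Visit 2 or 3, where the adverse-event review takes place. Only new, unrelated events are left.

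**Step 4: how many subjects.** The documents give no withdrawals by reason. The only related figure is the dropout allowance in section 6.2: 2 × 186 = 372 and 416 − 372 = 44, or 44/416 = 10.6%. It covers dropout for every reason and does not estimate these withdrawals.

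**The case against.** The strongest reply is that the text is ambiguous rather than categorical. Section 7.3 says discontinued or withdrawn, section 8.1 uses the list as a gate for the second dose, and section 9.0 lets the sponsor confirm that a subject continues. Sections 3.0 and 5.3 set safety follow-up in general terms, with no condition on meeting the blood-sampling window. A sensible site might well carry on asking. That stands as a reason to call this a clarification. It does not close the gap, because none of those passages mentions withdrawn subjects.

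It is also fair to say that many item 5 subjects simply do not attend, and for them the loss comes from non-attendance. That stands too. It is why the late attender at Visit 2, who is present and can be asked, is the clearest case.

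A reader might infer more than the documents support:

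- *That 11 of the 14 days after a dose (14 − 3 = 11; 79%) go unobserved because of 7.3.* That interval between the calls and the next visit is part of every subject's schedule. A non-attender would have it without item 5.
- *That all subjects under items 2 and 7 lose safety follow-up.* Their triggering events are followed, as shown above.
- *That section 5.7 withdraws users of the listed drugs for an immune-response reason.* The sentence "The decision would be based on whether the administered medication is known to interfere with the immune response" concerns other medications; the protocol gives no reason for the list.
- *That a steroid given for an allergic reaction under item 6 exposes a wider failure.* This is a constructed scenario, and a life-threatening reaction is an SAE that 10.5 follows in any event.
- *That pregnancy is handled in contradictory ways.* Exclusion criterion 12 ("If female patient will get pregnant after first vaccination") is a later event placed among entry criteria, while item 6 addresses it directly. That is a separate drafting matter.
- *That the analysis of incompletely followed subjects is missing.* This is commonly left to an analysis plan, and none is shown.

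**Conclusion.** The concern holds in a limited form and is minor. As written, dosed subjects can leave the study under 7.3 items 3 and 5 and under 5.7 without any express provision for collecting new adverse events to Day 28, while they stay in the safety set. For item 5 this gives a worse result than needed, because section 5.4 already does what the immunogenicity analysis requires. For items 2 and 7 the gap is confined to new, unrelated events.

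The effect is probably small and cannot be sized from the documents. The conclusion assumes that sites apply 7.3 literally and make no contact beyond what is scheduled. Where they review adverse events at the late visit or keep in touch, less is lost. The documents do not support reading the protocol as forbidding such contact: it is silent. Nothing here bears on the immunogenicity comparison.

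**What to change.** In section 7.3, separate *discontinued from further vaccination* from *withdrawn from the study*. Then:

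1. Make items 3, 5 and 7, and the medication rule in 5.7, stop further dosing and, where 5.4 applies, exclude the subject from the immunogenicity analysis.
2. State that any dosed subject who has not withdrawn consent stays in adverse-event and SAE contact, by telephone if needed, through the scheduled Visit 3 date.
3. State that the adverse-event review and diary collection due at a missed visit are done at the late visit or by telephone.
4. Keep the investigator's right to withdraw a subject in that subject's best interest.

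The cost is protocol wording and a few extra telephone contacts by field officers already in place. Sample size and the immunogenicity analysis do not change, and no subject becomes newly eligible for a second dose.

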## **8.0 STUDY DATA COLLECTION**

### **8.1 Study Visits:**

Following activities and assessments will be performed at each visit.

#### **Visit 1: Screening, Enrollment and first Vaccination Visit (Day 1)**

- a. Subject 1 year to 60 years age will be screened for this study.
- b. Written informed consent from subject/parents/legally accepted representative (LAR) will be obtained prior to performing any relative activity. Subject demography, medical history, prior medication and vaccination details, vital signs, physical examination will be done and results will be recorded in CRF pages.
- c. If the subject meets the inclusion and none of the exclusion criteria, he/she will be enrolled, allocated to one of the study arms as per randomization envelopes
- d. Urine Pregnancy Test for female patients who are of child bearing potential and sexually active.
- e. A blood sample of 4 ml will be withdrawn (for antibody titers) before administration of first vaccine dose.
- f. Subject will receive first dose of either Euvichol-Plus or Shanchol™ based upon the randomization in the Cohort 1 and 2. Concomitant Medication details will also be recorded.
- g. Subjects will be observed at the study site for 30 minutes after vaccination. Examination for any systemic reactions will be made and findings will be recorded in the CRF.
- h. Subject/parents/LAR of the subject will be instructed to evaluate systemic reactions and record the temperature at home for 3 days post-immunization (At day 0, 1, 2 and 3). Diary card will be issued for the filling the observations by the subject /parents/LAR
- i. Schedule next site visit after 2 weeks. Subject/parents/LAR will be instructed for his/her subsequent appointment for immunization.

#### **Visit 2: Second Vaccination Day 14 (+ 3 days after the first dose)**

- a. Any AE since the last vaccination will be recorded. Any unreported SAE since the last visit will also be recorded and reported by telephone/ facsimile/e-mail by the investigator as per regulatory requirements. Original Diary Card will be collected and data will be reconciled with the CRF.
- b. Vital Signs, Physical and clinical examination will be done and results will be recorded in CRF pages. Concomitant Medication and vaccination details will also be recorded.
- c. A blood sample of 4 ml will be withdrawn (for antibody titers) before administration of second vaccine dose.
- d. If subjects are not excluded for the second dose of the vaccination as per the withdrawal criteria mentioned in section 7.3, subject will be administered orally second dose of either of the Test or Comparator vaccine as per the treatment allocated at visit 1 in the Cohort 1 and 2. Subjects will be observed at the study site for 30 minutes after immunization. Examination for any systemic reactions will be made and findings will be recorded in the CRF.

- e. Subject/parents/LAR of the subject will be instructed to evaluate systemic reactions and record the temperature at home for 3 days post-immunization (At day 0, 1, 2 and 3). Diary card will be issued for the filling the observations by the subject/parents/LAR of the subject.
- f. Schedule next site visit after 2 weeks. Subject/parents/LAR of the subject will be instructed for his/her subsequent appointment.

### **Follow up 1 & 2 (Telephonic Visits)**

The appointed field officer will contact (email/phone/visit) the subject/parents/LAR after vaccination to determine the subject health status.

### **Visit 3: End of Study (EOS) visit Day 28 (+ 3 days after the second dose)**

- a. Any AE since the last vaccination will be recorded. Any unreported SAE since the last visit will also be recorded and reported by telephone/ facsimile/e-mail by the investigator as per regulatory requirement. Original Diary Card will be collected and data will be reconciled with the CRF.
- b. Vital Signs, Physical and clinical examination will be done and results will be recorded in CRF pages. Concomitant Medication and vaccination details will also be recorded.
- c. 4 ml of blood sample will be withdrawn for antibody titers.
- d. Complete all pending information on the CRF including study completion page.

### **8.2 Method of blood collection and storage**

Blood samples for antibody titers will be taken immediately before first and second vaccination and 2 weeks after the second dose of the study vaccine. Hence, 3 blood samples will be collected for each subject over the entire study period.

On each of the scheduled days, 4 ml of venous blood drawn from all the subjects will be collected in plain tubes. Clotted blood in the plain tube will be centrifuged to obtain serum. Serum obtained after centrifugation will be divided in two parts to be stored in two separate cryovial. At least 1.0 ml of the serum will be stored in one cryovial with the remaining serum transferred to the second cryovial. All cryovial containing serum for antibody analysis will be stored at or below - (minus) 20° C. One set of cryovial (containing 1.0 ml serum) will be sent to the central laboratory and the other will be stored at the site, which will be shipped to the sponsor on completion of the trial. The site laboratory assistant will be responsible for the labeling of the sera, labels will be provided by the sponsor. All serum samples will be sent to central laboratory with labels mentioning the protocol number, Enrollment ID of the subject, Subject initial and visit date (date of sample withdrawn).

### **8.3 Central Laboratory**

Analysis will be done at the designated laboratory i.e NICED Kolkata.

### **8.4 Schedule of events**

The summary of assessments performed during the trial is mentioned in Annexure –II.

## **9.0 PROTOCOL DEVIATIONS AND VIOLATIONS**

A protocol deviation is defined as failure to fully comply with the final study protocol approved by the Ethics Committee (EC).

The deviation can be classified further as:

- Protocol Violation - Serious non-compliance with the protocol
- Protocol Deviation - Less serious non-compliance which needs adequate documentation

All violations or deviations from the approved protocol should be documented. The following details will be captured:

- Description of deviation
- Date of deviation
- Date reported and by whom
- Decision of sponsor
- Authorization of waiver, if applicable

All protocol violations or deviations will be reported to the sponsor company/CRO immediately to confirm subject continuation or withdrawal from the study. If the sponsor company agrees to the subject continuing in the study a note to file must be made by site personnel and the study monitor.

In case of a deviation, the investigator will inform CRO and seek approval for continuation/discontinuation of the concerned subject. The Investigator should not deviate from the protocol. The EC will be informed of protocol deviations by the investigator, according to applicable regulations and the EC's established procedures. The EC must provide written agreement for any deviation prior to continuing with the study. Unless CRO has consented to any such deviations in writing, CRO will not assume any resulting responsibility or liability. In medical emergencies, prior approval for protocol deviations will not be required.

## **10.0 ADVERSE EVENT**

### **10.1 Adverse Event Monitoring**

Any adverse events or side effects will be elicited by recording the response to a standard question "Have you noticed any problems with the treatment".

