### **10.2 Adverse Event Documentation**

Recording of AEs will begin after the ICD is signed by the subject or subject/parent/LAR. Any medical event occurring before the first dose of the vaccine will be regarded as a pre-treatment administration event. All events occurring after the first dose and prior events that worsen any time after the first dose will be regarded as Treatment Emergent Adverse Events (TEAE).

Any AE occurring after providing the informed consent and until the last study visit will be recorded on the CRF. All TEAEs occurring during the study period will be followed up by the investigator until resolution or stabilization of the event or until the subject is lost to follow-up. This follow-up should be documented in the subject medical records and may be extended beyond the end of the study period.

An **Adverse Event (AE)** is defined as any untoward medical occurrence (including a symptom/disease or an abnormal laboratory finding) in a patient or clinical investigation subject administered a pharmaceutical product at any dose that does not necessarily have to have a causal relationship with this treatment. An adverse event can, therefore be any unfavorable and

unintended sign (including an abnormal laboratory finding, for example), symptom, or disease temporally associated with the use of an investigational product, whether or not considered related to the investigational product. This definition includes inter-current illnesses or injuries and exacerbation of pre-existing conditions.

**Adverse Event Following Immunization (AEFI):** This is defined as any untoward medical occurrence which follows immunization and which does not necessarily have a causal relationship with the use of the vaccine. The adverse event may be any unfavorable or unintended sign, an abnormal laboratory finding, a symptom or a disease.

The adverse events reported and as observed by the investigator will be filled in the case report form and maintained for the purpose of documentation.

The investigator must report adverse events which are clinically apparent, or in the investigator's opinion clinically significant, in the relevant part of the case report form.

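### The only scripted adverse-event question (Section 10.1) is narrower than the AE definition in Section 10.2, so unsolicited events may be under-reported

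*Supplement*

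**What the plan says.** Section 10.1 (Adverse Event Monitoring) is a single sentence. It makes the answer to one standard question, "Have you noticed any problems with the treatment", the means by which adverse events and side effects are elicited.

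Section 10.2 (Adverse Event Documentation) sets a wider target. An AE is an untoward occurrence "that does not necessarily have to have a causal relationship with this treatment", and it counts "whether or not considered related to the investigational product". The section adds: "This definition includes inter-current illnesses or injuries and exacerbation of pre-existing conditions". An adverse event following immunization is likewise "any untoward medical occurrence which follows immunization and which does not necessarily have a causal relationship with the use of the vaccine". CRF recording runs from consent to the last visit.

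Three further provisions show where these data are used:

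- Section 4.7 makes the safety comparison of the two vaccines the secondary objective, and Section 4.8 lists unsolicited events over Day 0-28 as a safety endpoint.
- Section 11.0 has the DSMB review 14-day post-vaccination safety data from the adult cohort before it recommends on enrolling children, and later the same data from the children.
- Section 6.3 states: "Trial subjects and investigator will be aware of treatments received".

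**The concern.** A person asked about problems with the treatment can truthfully answer no after an injury or a respiratory infection on Day 9, if they do not connect it with an oral vaccine. Section 10.2 nevertheless requires that event on the CRF. The wording moves a first causality judgement to the respondent, whereas Section 10.3 places that judgement after reporting. Its scheme has categories for coincidental events and for indeterminate events that may be a new signal. These are the events a layperson is least likely to blame on the vaccine, and the scheme can classify only what reaches the CRF.

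What is at stake is the completeness of unsolicited events. Solicited reactions are prelisted, graded and collected by diary, so the wording of this question hardly touches them. If unsolicited events are lost equally in both arms, absolute rates are too low, which matters for the DSMB's view of the adult data. If the loss differs by arm, the comparison is distorted too. Respondents know whether they received the new or the established product, so a difference is possible.

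**Working it through.** The protocol gives no figure on this point to reproduce. The check is mainly a comparison of text, followed by an illustration under stated assumptions.

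**Step 1: scope of the question against the definition.** Section 10.1 ties the answer to the treatment. Section 10.2 removes causality from both the AE and the AEFI definition and includes intercurrent illness and injury. The prompt is narrower than what must be recorded.

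**Step 2: can other routes fill the gap?**

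- *Visits 2 and 3 (Section 8.1, item a of each).* All AEs since the previous dose are to be recorded, with no attribution condition. This covers the whole interval, but it says what to record, not how to ask.
- *Section 10.3.* Events that staff observe or families volunteer must be entered. For an event that has resolved, this depends on what the family says.
- *Telephone follow-up (Section 8.1 and the Protocol Summary).* Contacts ask neutrally about health, but run for three consecutive days after each dose.
- *Diary.* The Protocol Summary tells subjects to record adverse events after dosing and sets no end day. The visit instructions are narrower: they ask families to note systemic reactions and to "record the temperature at home for 3 days post-immunization". Section 10.2 defines unsolicited events as those outside the diary's prelisted conditions. The diary card is not shown, so how far it covers later events is unsettled.
- *Examination, vital signs and concomitant-medication review (Table 1).* These are independent of the question and will pick up some events, mainly those still visible or treated.

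**Step 3: the days without a neutral scripted prompt.** The calls end at Day 3 and Visit 2 is at Day 14 (+3 days). Day 4 to Day 14 is 14 − 3 = 11 days, or 17 − 3 = 14 days at the end of the window. The same pattern follows dose 2. Most of the DSMB's 14-day window falls in this stretch.

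**Step 4: what a loss would do (illustration only).** Let p be the true unsolicited-event risk, equal in both arms, and let c be the fraction captured by all routes together. Then observed risk = p × c, the between-arm difference = p × (c₁ − c₂), and the ratio = c₁ / c₂. The 208 subjects per arm come from Section 6.2. The values p = 5%, 10%, 20% and all values of c are assumptions. The 2.30% (69 of 2,999) in Section 4.5 cannot calibrate them, because it counts adverse drug reactions, which are already attributed events.

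- c = 50% in both arms: observed 2.5%, 5%, 10%. Difference 0, ratio 1.0.
- c = 80% against 60%: 4% v 3%, 8% v 6%, 16% v 12%. Ratio 0.80/0.60 = 1.33; excess 208 × 0.01, 0.02, 0.04 = 2.1, 4.2, 8.3 subjects. The chance of p<0.05 in that direction is about 8%, 12%, 22% (normal approximation, two-sided 0.05).
- c = 90% against 50%: 4.5% v 2.5%, 9% v 5%, 18% v 10%. Ratio 0.90/0.50 = 1.8; excess 208 × 0.02, 0.04, 0.08 = 4.2, 8.3, 16.6 subjects. The chance is about 20%, 36%, 65%.

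Equal loss understates both rates and favours neither arm. A spurious difference needs capture to differ by arm.

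**The case against.** The strongest reply is that Section 10.1 is only an opening prompt. The duty to record lies in Section 10.2 and in the visit procedures, and neither carries an attribution condition. Several routes bypass the question altogether, and nothing tells respondents to withhold events they think unrelated. The CRF and diary card, which may hold better wording, are not shown. Safety is a secondary objective with no stated hypothesis, margin or between-arm test for AEs. Most of this stands, and it limits the point.

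A reader might infer three stronger things that the documents do not support:

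- *That Section 10.1 flatly contradicts Section 10.2.* A narrow prompt does not alter the definition or the duty to record. The two are misaligned.
- *That this question is the main source of unsolicited events after Day 3.* The visit recording rule covers those days, and the general diary instruction has no end day.
- *That the safety comparison is biased.* No figure in the documents shows that capture differs by arm, and open-label knowledge makes a difference possible, not demonstrated.

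What the reply does not remove is that Section 10.1 presents this wording as the way adverse events are elicited, and that no other passage gives staff a neutral script for the later days. Staff who follow it as written may miss events that Section 10.2 wants.

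**Conclusion.** The point holds as a risk of under-ascertainment. The one scripted question in the protocol as shown is narrower than the AE and AEFI definitions, and the other routes offset this only in part from about Day 4 to the next visit. Loss of unsolicited events is plausible, and a between-arm difference is possible because the trial is open label. The documents fix neither its size nor its direction; the illustrative figures rest wholly on assumed risks and capture fractions and are not estimates for this trial. Solicited reactions are largely unaffected, and the primary immunogenicity endpoint is not affected. This is a modest defect in safety data collection that should be corrected, not one that undermines the trial.

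**What to change.** Replace the question in Section 10.1 with a neutral one, for example: *Have you (has your child) had any health problem or change in health since the last vaccination or contact?* Ask it word for word in both arms at each visit and each telephone contact, and leave causality to the assessment in Section 10.3. Carry the same wording into the CRF and the call script.

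The cost is one sentence in the protocol with matching edits to those two documents, and slightly more minor events recorded. No clinical rule changes. The fix does not remove every open-label effect, since respondents will still know their vaccine when they answer; it removes the invitation to attribute before reporting.
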